### Study interventions

#### Intervention procedures

Children receive the interventions in groups or “classes” of ~15-18 children, 1 hour and 30 minutes per week (three OC groups and three VA groups). The interventions will start in March 2024 (wave 1, one group per condition) and in September 2024 (wave 2, two groups per condition). About 50 children will participate in each experimental condition (OC, VA, CG), so 150 children in total. Accounting for an attrition of maximum 30%, final analyses would include a minimum of 35 children per group, ensuring adequate statistical power (see Statistical analysis plan and sample size calculation).

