## Statistics and methodology

### Statistical analysis plan and sample size calculation

The research statistician of the host institute of the principal investigator will assist with the behavioral analyses. Experts in MRI data analysis, machine learning, and multimodal data integration within the team will supervise both MRI data analysis and the combined multivariate analysis of behavioral and MRI data.

*Sample size*: We computed sample size separately for our main behavioral outcome (WM) and for fMRI and structural MRI data. Our sample size will consist of 50 children per group, and we account for an attrition of 30%, so for the final analyses, we will dispose of minimum 35 children per group.

For our main behavioral outcome WM: Based on our previous behavioral study on OC [1]: with an alpha=0.05 and power=0.80, the projected sample size needed to reach a similar effect size (GPower 3.1) *n*=48 is the total for a simple between-group comparison, thus *n*=24 per group.

For fMRI data: A cross-sectional study comparing visual working memory networks of two groups of 19 ADHD and 14 healthy children (8-12 YOA) using a similar design [104] obtained activation maps within groups and between groups with numerous clusters surviving to correction for multiple comparisons at *p*<0.05 FWE (family-wise error).

For structural MRI data: A study showed large developmental brain plasticity changes in gray/white matter volume and fractional anisotropy (FA) at the whole-brain level (*p*<0.05 corrected for multiple comparisons) using a longitudinal design in a group of 24 adolescents [105].

To address the issue of selective dropout, we adjusted our participant numbers to account for an anticipated attrition rate of 30%, while still meeting the necessary sample size criteria, computed above.

A longitudinal randomized controlled trial (RCT) with three measurement time points and sufficient sample sizes offers increased statistical power and helps mitigate the risk of false positive findings commonly associated with smaller, non-randomized studies.

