For the brain data we will use univariate and multivariate analysis methods. Individuals’ intensity of training, progress, demographic characteristics, physical aerobic fitness and appreciation of the courses will be considered.

Step 3: we will analyze all data in a multivariate data-driven thus exploratory way. Separately analyzing behavioral data and several kinds of brain imaging data, cross-sectionally and over time, provides extremely valuable information on these data. Additionally, combining diverse behavioral and multimodal brain MRI data within data-driven multivariate analyses may unravel hidden “covert” relationships [108, 109]. These advanced analyses will encompass two main axes. The 1^st^ axis will be concerned with group inferences, asking “what intervention-related changes can be observed on imaging data at the group level?”, while the 2^nd^ axis will be concerned with individual prediction: “Can imaging features predict behavioral outcomes at the individual level?” To this end, we will consider joint analyses of imaging data (structural connectivity, functional connectivity data considered together).

In the 1^st^ axis (group-level analysis), we will use two methods which have been used successfully on multimodal brain imaging data, each carrying different assumptions about linearity of relationships and distribution of variables: multimodal Independent Component Analysis (ICA) [108, 109] on the one hand, and Partial Least Squares (PLS) [110–112] on the other. We detail these methods below.

Joint, fusion, and linked ICA [113, 114] are variants of ICA that allow combining different types of data such as functional and structural neuroimaging data. These analyses could reveal joint changes in different imaging modalities (i.e. covariations in functional and structural connectivity measures) and allow to investigate differences between our three groups [108, 113].PLS is another powerful technique that can identify components of multivariate relationships between imaging and behavioral data [111, 115], notably PLS correlation models [111]. PLS and sparse PLS may reveal hidden relationships between battery tests and MRI measurements before and after the regimens (OC and VA) and show whether these relationships differ between the groups. Implementations of these approaches are publicly available in addition to several in-house extensions that allow using them in the most flexible way, including machine learning [74, 116].

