In the 2^nd^ axis (individual prediction), we will attempt to predict the difference in behavioral outcomes (digit span, auditory/tonal, and visual WM) from the difference in connectomes^3^ between time points T0 and T2. The control group will allow discarding developmental connectivity differences that are not related to our interventions or not meaningful for predicting working memory. Here, we will leverage recent advances in graph-based machine learning, particularly graph neural networks (GNN). We will use each subject’s connectivity values (either in the whole brain, or in specific functional networks of interest (CEN, SN)) as input to train a GNN model to predict the behavioral scores. The scores can be predicted one by one, or jointly by using a multi-output network (see Fig. 1 for an overview of the analyses). To improve performance, we will use a technique called *transfer learning*, by pre-training the GNN model using related tasks and scores from other cohorts, and then fine-tune using our own data. The team of [name] successfully developed related transfer learning approaches on other datasets. Further, we will use our newly developed graph data augmentation technique^4^ to ensure that sample size is not an issue. Using a GNN model allows us to perform this analysis for both the structural and functional connectomes, where functional connectomes are obtained either from resting-state or from task-based connectivity.

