**Fig. 1 Fig1:**
[figure not shown]
Data analysis overview This table summarizes steps and methods used to achieve our ultimate goal i.e., the prediction of the main behavioral outcome: working memory improvement and development (WM: working memory; ANCOVA: Analysis of Covariance; LME: linear mixed model equations; GLM: general linear model; MRI: magnetic resonance imaging; ICA: independent component analysis; ICAPs: innovation-driven co-activation patterns, PLS: partial least squares; GNN: graph neural networks)

Significance level will be strictly controlled using false discovery rate special techniques for multiple comparison correction for univariate and multivariate analyses involving behavioral, MRI and combined behavioral and MRI data [117].

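### Graph data augmentation cannot remove the sample-size limit on individual prediction: precision still rests on about 105 children

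*Protocol article*

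**What the plan says.** Under Planned statistical analyses, the second axis of Step 3 asks "Can imaging features predict behavioral outcomes at the individual level". The target is change between T0 and T2: "we will attempt to predict the difference in behavioral outcomes (digit span, auditory/tonal, and visual WM) from the difference in connectomes". Two aids to training are named. One is pre-training on other cohorts followed by fine-tuning on the trial's own data. The other is a newly developed graph augmentation technique, which is there "to ensure that sample size is not an issue". The technique carries a footnote whose text is not in the material shown.

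On numbers, the sample-size section plans 50 children per group with 30% attrition, and Intervention procedures says that "final analyses would include a minimum of 35 children per group". The sample-size section treats behavioural WM, fMRI and structural MRI separately. It does not address individual prediction.

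On weight, Step 3 is labelled exploratory. The caption of Fig. 1, however, describes the "steps and methods used to achieve our ultimate goal i.e., the prediction of the main behavioral outcome", namely improvement and development of WM.

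**The concern.** The sentence claims a property that augmentation does not have. A synthetic graph derived from a child's scan carries that child's outcome and information derived from that child's data. Making many such graphs may help a flexible network to fit more stably. It does not increase the number of independent pairs of brain change and WM change against which the predictions are judged, and that number governs how precisely accuracy can be known.

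This matters because the assurance is the only statement about sample size for an analysis that the figure caption calls the ultimate goal. A reader who accepts it would take a moderate correlation as established at the level of the individual child, when the data could not separate a weak predictor from a fairly good one.

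**Working it through.** **Step 1. Reproduce the plan's own figure.** Enrolled: 50 per group. Attrition: 30%. Then 50 × 0.70 = 35 per group, as the protocol states, and 35 × 3 = 105 over three groups. The two art groups alone give 35 × 2 = 70. With no attrition at all, the total is 150.

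**Step 2. Precision of a predicted-versus-observed correlation.** Use the Fisher z interval, with one held-out prediction per child:

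- z = atanh(r); SE = 1/√(n − 3); limits = tanh(z ± 1.96 × SE).
- For r = 0.3, z = 0.310.
- n = 105: SE = 1/√102 = 0.099; z limits 0.115 and 0.504; r limits 0.11 and 0.46.
- n = 35: SE = 1/√32 = 0.177; z limits -0.037 and 0.656; r limits -0.04 and 0.58.

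| Children tested | 95% interval, r = 0 | 95% interval, r = 0.3 |
|---|---|---|
| 35 (one arm) | -0.33 to 0.33 | -0.04 to 0.58 |
| 70 (two art arms) | -0.23 to 0.23 | 0.07 to 0.50 |
| 105 (planned minimum) | -0.19 to 0.19 | 0.11 to 0.46 |
| 150 (no attrition) | -0.16 to 0.16 | 0.15 to 0.44 |

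The value r = 0.3 is an assumption used to show the width; the protocol gives no expected accuracy.

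**Step 3. What counting synthetic graphs as sample would do.** Suppose ten graphs per child (an assumption; the protocol gives no number). Then 105 × 10 = 1,050 graphs, and the formula would return SE = 1/√1047 = 0.031 instead of 0.099. The gain would be false, since there are still 105 children.

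**Step 4. Illustrative simulation.** Ridge regression stood in for the network, with 500 pure-noise features, 5 or 10 noisy copies per child, copy noise of 0.5 or 1.0 SD, 5-fold validation and 30 repetitions. With 105 children, folds split by child and testing on real data only, mean r was between -0.04 and -0.01, both with and without augmentation. Its SD was 0.09 to 0.15 with augmentation and 0.10 to 0.15 without. These SDs are close to or above the Fisher value of 0.099, so the intervals in Step 2 are, if anything, a little narrow.

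**The case against.** The strongest reply is that the sentence is about training. It follows the passage on transfer learning and speaks of improving performance, and nothing in the article says that augmented graphs will be counted as children in any interval or test. Augmentation can reduce overfitting in a nonlinear network, and pre-training does bring in outside information. The simulation cannot refute that: adding Gaussian noise to the features of a ridge model acts roughly like extra penalty, so little change is expected by construction. All this stands. It does not rescue the wording, because better training leaves the number of children available for testing unchanged, and pre-training adds no child to the test of two-year change in this trial.

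Two stronger readings are tempting, and the documents do not support either.

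- A reader might infer that augmented copies of one child will fall in both training and test folds and inflate accuracy. If they did, the effect could be large: in the pure-noise simulation with 105 children, copies split at random gave an apparent mean r of 0.74 to 0.95. But the protocol does not say that it will split this way. Fold structure is commonly left to a fuller analysis plan, and the footnote on the technique is not shown. Leakage is a risk to guard against, not a stated error.
- A reader might infer that arms are pooled so that arm and age drive both changes. The article does not state such pooling. It gives the control group the role of discarding developmental differences unrelated to the interventions, and elsewhere it plans covariates for age, gender, socioeconomic background and baseline WM.

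It is also fair to say that the step is exploratory, that the authors only undertake to attempt the prediction, and that the caption calling it the ultimate goal covers every analysis step.

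**Conclusion.** The assurance is wrong as stated and should go. Augmentation may regularise the network, but the effective sample for judging prediction is the number of real children: 105 at the planned minimum, fewer if arms are assessed separately. At that size an estimated r of 0.3 is compatible with about 0.11 to 0.46, and in one arm of 35 with -0.04 to 0.58. Even with no attrition the interval would be 0.15 to 0.44.

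These figures assume one independent held-out prediction per child and the Fisher approximation. They do not depend on the augmentation algorithm, the number of copies or the network.

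Severity is minor. The claim sits in an exploratory step, and the Step 2 linear mixed model comparisons of WM between groups do not rely on it.

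**What to change.** - Delete the assurance. State instead that augmentation is used to regularise training, that the effective sample is the number of children (about 105), and that this is a limitation of the exploratory prediction step.
- State that folds are split by child, that augmented graphs are used only for training, and that testing uses unaugmented data.
- Report out-of-sample r or R² with an interval computed over children.
- Report it beside a benchmark model using arm, age and T0 WM, so that the gain attributable to imaging can be seen.

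The cost is a few sentences and slightly more computing. The stated accuracy may look less favourable and its interval wider. Recruitment, interventions and the Step 2 analyses do not change.

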**Fig. 1 Fig1:**
[figure not shown]
Data analysis overview This table summarizes steps and methods used to achieve our ultimate goal i.e., the prediction of the main behavioral outcome: working memory improvement and development (WM: working memory; ANCOVA: Analysis of Covariance; LME: linear mixed model equations; GLM: general linear model; MRI: magnetic resonance imaging; ICA: independent component analysis; ICAPs: innovation-driven co-activation patterns, PLS: partial least squares; GNN: graph neural networks)

Significance level will be strictly controlled using false discovery rate special techniques for multiple comparison correction for univariate and multivariate analyses involving behavioral, MRI and combined behavioral and MRI data [117].

### Handling of missing data and drop-outs

#### Handling of missing data

Common approaches, like substituting missing data by the group mean, induce the risk of reducing statistical variability and study validity. In consequence, we will impute missing values using the regularized iterative Principal Component Analysis (PCA) algorithm developed by Josse, Husson and Pagès [118], implemented in the R software.

We will prevent drop-outs as much as possible by verifying at T0 the capacity of the child to pass the behavioral tests and MRI scans (psychological or physical problems). If a child fails to meet the requirements of the psychometric tests and/or MRI measurements, they will not be eligible to participate. This exclusion will be explicitly stated in the informed consent form.

We have multiple means to assess and facilitate children's adaptation to the MRI environment: 1) we prepared a video of a child undergoing MRI scanning in the BBL for the families to watch beforehand, 2) the BBL's virtual reality facility, "MRI Adventure", may prepare the children for the MRI setting, and 3) a mock scanner at the principal investigator's host institution will help the children to evaluate their comfort in the MRI environment.

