### Primary and secondary endpoints

Primary Endpoint: Improve WM performance through OC and to a lesser extent through VA interventions, as assessed by psychometric testing and fMRI tasks, in primary school children of 6-8 years at the start, following them over two years of intensive OC vs. VA group-interventions, as compared to baseline data (representing progress) and to the CG data (representing natural development). The rationale for the selection of WM was explained in *1.3.2.*

Secondary Endpoints:Identify significant changes in structural and functional brain plasticity, i.e. biomarkers (brain features), comparing 1-year and 2-year values to baseline values (i.e. progress) of both art interventions and to the CG values (natural development).Establish significant correlations between brain plasticity and EF performance change, comprising WM, following the two interventions, particularly MIP (OC), after one and two years of interventions, compared to baseline and to the CG values.Create a comprehensive data-driven model of child interrelated brain and EF development over the first two years of their academic curriculum, with and without additional cognitive enrichment (OC vs. VA vs. CG).Within the context of this comprehensive model of EF, explore how artistic enrichment may influence the typical transition from a more unified to a more multifaceted EF structure around age eight, comparing these findings against a minimally enriched CG [18, 20].

*Baseline factors* that may influence the endpoints are, amongst others, age, gender, socioeconomic background, and WM performance at baseline. These confounding factors will be partially controlled for through the stratified randomization and also in the statistical analyses (by means of covariates).

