#### Planned statistical analyses

Step 1: we will study relationships between EF and brain data collected at baseline for all participants based on a priori hypotheses and also in an exploratory way, using repeated measures Analysis of Covariance (ANCOVA), general linear models (GLM), correlations, and regression analyses. Apart from verifying a priori hypotheses, an additional goal is to identify potential confounding factors affecting our main outcome: EF, and particularly WM performance. Those confounding factors include socio-economic status, extra-curricular activities, aerobic physical fitness, and sleep. Apart from studying the influence of these factors on the outcomes, they also allow nuisance factor control, which will allow to objectively evaluate the OC and VA impact on EF in the following steps.

Brain data will be pre-processed and analyzed using in-house script routines calling the last versions of the standard neuroimaging software pipelines (e.g. Statistical Parametric Mapping 12 (or later version if released; https://www.fil.ion.ucl.ac.uk/spm/). We will generate a population-specific brain template. Individual brains and activation maps will be normalized on this template, critical for the validity of longitudinal brain plasticity results [106].

Step 2: we will examine and compare the development in both experimental groups and the CG over time for the comprehensive set of EF and brain data separately (T0 vs. T1 vs. T2). We will use linear mixed models (LMMs) with the open source software R [107] to evaluate the longitudinal effects for all behavioral variables separately, comparing all three groups over two years. LMMs are flexible, powerful, statistical models that can consider several levels of clustering, continuous and qualitative explanatory variables, as well as unbalanced data (pertinent if attrition differs per group). For testing specific hypotheses, we will add specific brain data in those LMMs (f.i. WM associations with CEN functional connectivity).

Near transfer scores closely representing direct benefits from the art interventions on the trained domains (musicality: IMMA [86, 87], visuo-spatial aptitude: the cubes test [84], teacher’s judgements, ratings by independent judges; see Table 3) will be analyzed in the same way. The results allow evaluating individual learning and the effectiveness of the courses.

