#### Attrition / drop-outs

Ultimate target: a total of at least 35 participants at T2 in each group (after the 2-year interventions)

Anticipating an attrition of 30% we will recruit approximately 150 participants, allowing to reach the final number of 35 individuals per group, which is necessary to reach sufficient statistical power (see section "Statistical analysis plan and sample size calculation").1^st^ experimental group Orchestra in Class OC: *n* = 502^nd^ experimental group Visual Arts: *n* = 50Active control group "Culture" CG: *n* = 50Total number of recruited participants ready to participate: 150

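### The PCA imputation has no stated limit, arm term or allowance for imputation uncertainty; the Step 2 mixed models do not need it, and it does harm if dropouts' missed visits are filled

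*Protocol article*

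**What the plan says.** The section *Handling of missing data* objects to group-mean substitution because such approaches "induce the risk of reducing statistical variability and study validity". It concludes that "we will impute missing values using the regularized iterative Principal Component Analysis (PCA) algorithm", as implemented in R. It does not say which variables, visits or analysis steps this covers, how many imputations are made, whether noise is added, or whether the arm enters.

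Under *Planned statistical analyses*, Step 2 compares the three groups over T0, T1 and T2 with linear mixed models (LMMs). One reason given for them is that they can take account of several levels of clustering, different kinds of explanatory variable, "as well as unbalanced data (pertinent if attrition differs per group".

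On numbers, *Intervention procedures* states "About 50 children will participate in each experimental condition (OC, VA, CG), so 150 children in total", and that "final analyses would include a minimum of 35 children per group". *Statistical analysis plan and sample size calculation* says "we account for an attrition of 30%, so for the final analyses, we will dispose of minimum 35 children per group". *Attrition / drop-outs* sets the target as "a total of at least 35 participants at T2 in each group".

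One secondary endpoint is to "explore how artistic enrichment may influence the typical transition from a more unified to a more multifaceted EF structure" around age eight.

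**The concern.** There are three difficulties.

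- **The remedy shares the fault it is meant to cure.** Plain regularised iterative PCA replaces each missing cell with a fitted value shrunk towards the low-rank structure. The fill has no residual scatter. Once treated as observed, it understates variability, as a mean fill does.
- **Step 2 does not need it.** An LMM fitted by likelihood uses every observed record, including those of children seen only at T0 or at T0 and T1. Filling outcomes beforehand adds no information.
- **The article does not settle who is filled.** The imputation sentence has no limit, and the parent heading covers both missing data and drop-outs. The sample-size text counts 35 per arm. A reader cannot tell whether the T2 analysis holds about 35 observed children per arm, or 50 of whom up to 15 have filled scores.

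At stake is the primary working-memory comparison between arms, which could be pulled towards zero or given too small a standard error. Low-rank fills also follow the fitted components, so they tend to raise correlations between tests. The EF-structure endpoint depends on those correlations.

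**Working it through.** **Inputs from the article.** About 50 children per arm and 30% attrition: 50 x 0.70 = 35, which reproduces the stated figure. The article prints no dilution or type I error figure for the imputation, so there is nothing further to reproduce.

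**Assumptions, not in the article.** Within-test correlation over time 0.5-0.7; between-test correlation 0.25-0.4; 3 to 8 tests; two components; dropout completely at random; a true OC-CG difference of 0.80 SD at T2. Informative dropout was not examined.

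**Closed-form bounds.** Let p be the observed fraction at T2, n the number per arm and d the true difference.

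- *Fill carries no arm information.* Each arm mean becomes p x (arm mean) + (1 - p) x (common mean). The difference is p x d, or 0.70 d with 30% filled: 30% dilution.
- *Fill at the arm mean.* The reported variance of an arm mean is about p x sigma^2 / n; the real one is sigma^2 / (p x n). The ratio of reported to real SE is p = 0.70. Nominal 5% type I error becomes 2 x (1 - Phi(1.96 x 0.70)) = 2 x (1 - Phi(1.372)) = 17.0%. The same formula gives 11.7% with 20% filled, 7.8% with 10% and 6.3% with 5%.

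**Simulation.** 3 x 50 children, three visits, regularised iterative PCA, then an OC-CG test on the filled data (500-600 null runs and 200 effect runs in the main settings).

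| Filled | PCA set-up | Share of effect kept | Type I error |
|---|---|---|---|
| 30% at T2 | pooled over arms | 0.70-0.79 | 3-6% |
| 30% at T2 | within arm | 0.97-1.02 | ANCOVA 13-17%; change score 10-13% |
| 30% at T2 | arm indicators in matrix | 0.79-0.86 | ANCOVA 6-10% |
| 20%, lost before T1 | pooled / within arm | 0.82 / 0.99 | 4.2% / 11.8% |
| 10%, lost before T1 | pooled / within arm | 0.91 / 0.97 | 4.8% / 8.0% |
| about 5% scattered gaps | pooled | 0.93-0.97 | about 5-6% |

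In the first row the share depends on when children leave: 0.70 if all go before T1, 0.71-0.74 if half do, 0.74-0.79 if only T2 is lost.

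**Under the article's own model.** A random-intercept LMM fitted by REML, with 6 tests, retest r 0.60, inter-test r 0.38, and 14% missing at T1 and 30% at T2, gave:

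- *Observed records:* estimate 0.82 for a true 0.80; type I error 5.2% (600 runs).
- *Pooled fill:* estimate 0.58, so 1 - 0.58/0.80 = 28% dilution; type I error 4.8%.
- *Fill by arm:* estimate 0.82, mean reported SE 0.168 against a real SD of 0.207; type I error 10.3%. As a check, 0.168/0.207 = 0.81 and 2 x (1 - Phi(1.96 x 0.81)) is about 11%.

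A second LMM run gave about 12% for the fill by arm. Another, on observed records only, kept 100% of the effect with 6.8% rejection (250 runs, Monte Carlo SE about 1.4 points). Complete-case ANCOVA gave 3.5-6.7%.

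**EF structure.** With whole visits filled, one set-up moved the mean inter-test correlation at T2 from 0.38 to 0.44. The shift is small and comes from a single setting, so I use it for direction only.

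**The case against.** The strongest reply is that the article never says dropouts are imputed. Three sections count 35 per arm, *Attrition / drop-outs* does not mention imputation, and the LMM is chosen partly because it accepts unbalanced data. On that reading attrition is left to the LMM and PCA fills only isolated gaps, where the table shows little harm. The article is also condensed: the number of imputations, added noise and the role of arm may be set out in a plan that is not shown.

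Much of this stands, and it rules out several stronger readings that a reader might infer:

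- *That nearly a third of T2 values will be synthetic, each filled once.* The text neither says nor excludes this. Single filling is inferred from the named algorithm.
- *That type I error will be 16-18%.* That is the top of the range and comes from ANCOVA; Step 2 names LMMs, for which the figure is about 10-12%.
- *That the choice lies between dilution and inflated error.* Arm indicators in the PCA matrix give a milder amount of each.
- *That filling leaks test children into the graph neural network.* The article does not describe how imputation relates to the training split, so this is conjecture.
- *That EF structure is pushed towards unity more in the arm with more dropout.* No arm-specific dropout rate is stated, and the claim was not tested.

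What the reply does not remove is that the imputation sentence is unlimited, that the method it names has the weakness it is meant to avoid, and that outcome filling serves no purpose in Step 2.

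**Conclusion.** The point holds as a badly fixed method together with sections that need reconciling. It does not show that the analysis will be biased. The size is conditional. If the 30% lost at T2 are filled and treated as observed, expect one of the following:

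- 21-30% dilution with PCA pooled over arms;
- type I error of about 10-12% by LMM (13-17% by ANCOVA) with PCA run by arm;
- 14-21% dilution with 6-10% type I error when arm indicators are in the matrix.

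If only about 5% of values are scattered gaps, pooled dilution is 3-7% and type I error about 5-6%. All simulated figures rest on the assumed correlations and on random dropout. Fitting the LMM to observed records avoided both harms in the same simulations, at essentially no cost.

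**What to change.** 1. In *Handling of missing data*, say whether the missed visits of children who leave are imputed, and reconcile this with the 35 per arm in *Intervention procedures*, *Statistical analysis plan and sample size calculation* and *Attrition / drop-outs*.
2. For Step 2, state that the LMMs are fitted by REML to all observed T0, T1 and T2 records of all randomised children, without imputing outcomes.
3. For Step 3 methods that need a complete matrix, use the multiple-imputation version of the PCA method, take arm into account, and carry the between-imputation uncertainty into the results.
4. Do not impute wholly missed visits for the EF-structure endpoint.

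The cost is wording and a little more computing in Step 3. Step 2 becomes simpler, and neither data collection nor sample size changes.
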